##### Secondary outcomes measures

Continuous abstinence at the 6‐month follow‐up, defined as not having had more than five cigarettes in the period from 2 weeks after baseline to the follow‐up, in line with the Russell Standard [40]. Self‐reported smoking abstinence at 2–4 weeks from baseline or target quit date (whichever is later). Fifty percent smoking reduction at 1‐ and 6‐month follow‐ups, calculated by the reduction in self‐reported cigarettes per day from baseline. Number of unsuccessful quit attempts at the 1‐ and 6‐month follow‐ups.

Mental health symptoms assessed by Patient Health Questionnaire‐9 (PHQ‐9) [43] and General Anxiety Disorder‐7 (GAD‐7) [44], general mood, physical symptoms assessed by the Mood and Physical Symptoms Scale (MPPS) [45, 46], and experience of adverse events at the 1‐ and 6‐month follow‐ups, similar to previous research [23].

Cost‐effectiveness of the intervention based on health economics measures outlined below.

The fidelity of intervention implementation and satisfaction with the intervention at the 1‐ and 6‐month follow‐ups will be based on questions related to e‐cigarette use in the past month as well as a question to assess whether the e‐cigarette used in the last month was the device provided to intervention participants as part of the study.

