#### Primary analysis

The effect of treatment on the primary outcome (CO‐verified 7‐day abstinence rates at the 6‐month follow‐up) will be analysed by a mixed‐effect (multilevel) logistic regression model with fixed treatment and a random intercept for site, included to allow for any site‐level variation in treatment effect. We will employ a likelihood ratio (LR) test to assess the significance of including the random site effects by comparing the mixed‐effects model with a model including only fixed effects. In addition, we will calculate the intraclass correlation coefficient (ICC) to quantify the proportion of variance in the primary outcome attributable to differences among clinical sites.

Secondary outcomes at the 1‐ and 6‐month follow‐ups will also be analysed as described above if they are binary, or with mixed effects (multilevel) linear regression adjusting for site‐level variation if they are continuous numeric variables. Mean difference will be reported. For regressions, we will check the assumptions of normality of the residuals.

We will use a repeated measures analyses to examine changes in cigarette consumption (a reduction of ≥50%) and mental health symptoms across baseline, and the 1‐and 6‐month follow‐ups. For continuous mental health symptom scores, we will use a multilevel linear regression model. We will verify the assumptions of normality and homoscedasticity of the residuals using quantile–quantile (QQ) plots and residual versus fitted plots. If these assumptions are not met, we will apply appropriate transformations (e.g. log transformation for positively skewed data). For the binary outcome of a ≥50% reduction in cigarette consumption, we will use a mixed‐effects logistic regression model. We will assess for overdispersion by comparing the residual deviance with the degrees of freedom and will consider alternative models, such as negative binomial regression, if overdispersion is present. Our models will incorporate fixed effects for the intervention group, time (treated as a categorical factor) and their interaction to assess differential changes between groups over time. To account for individual variability, we will include random intercepts for each participant and clinic site.

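### The random-intercept repeated-measures model for PHQ-9 and GAD-7 imposes equal correlation over unequal visit gaps; if correlation falls with time, the 6-month change contrast gets too small a standard error

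*Protocol article*

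**What the plan says.** In the Protocol article, Analysis, Primary analysis, the third paragraph sets out a repeated-measures analysis of "mental health symptoms across baseline, and the 1‐and 6‐month follow‐ups". The model type is given: "For continuous mental health symptom scores, we will use a multilevel linear regression model". So are the fixed effects: "Our models will incorporate fixed effects for the intervention group, time (treated as a categorical factor) and their interaction", and the random effects: "To account for individual variability, we will include random intercepts for each participant and clinic site".

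No random slope, residual correlation structure or robust standard error is named. The planned diagnostics are limited: "We will verify the assumptions of normality and homoscedasticity of the residuals", by quantile–quantile and residual-versus-fitted plots, with transformation as the remedy.

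The paragraph before it also covers these scores. Secondary outcomes at 1 and 6 months are to be analysed "with mixed effects (multilevel) linear regression adjusting for site‐level variation if they are continuous numeric variables", with a mean difference reported. PHQ-9 and GAD-7 are listed there as secondary outcomes under Secondary outcomes measures.

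**The concern.** A random intercept per participant with independent residuals is a compound-symmetry model. Two scores from the same person share one covariance whichever two visits they come from, and every visit has the same variance. The site intercept does not relax this, because it is constant over a participant's visits and cancels from any change from baseline.

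The visits fall at 0, 1 and 6 months. Symptom scores one month apart may well correlate more strongly than scores five or six months apart. The model pools the three correlations into one, so with complete data it gives the 1-month and 6-month change contrasts the same standard error. If the correlations differ, at least one of those standard errors is generally wrong.

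The interaction is there for a stated purpose, "time (treated as a categorical factor) and their interaction to assess differential changes between groups over time", and mental health at 6 months is a secondary objective. An interval that is too narrow at 6 months could suggest a mental-health difference that is not there. One that is too wide at 1 month could hide a real difference. The planned plots would not reveal a wrong correlation pattern, and a transformation would not cure it.

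**Working it through.** **Inputs from the Protocol article.** 308 per group (Sample size); alpha 0.05; visits at 0, 1 and 6 months; random intercepts for participant and site. The article states no standard deviation, between-visit correlation, standard error or power for PHQ-9 or GAD-7, so it has no figure of its own to reproduce here.

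**Assumed inputs.** Equal variance v at each visit, complete data, and correlations r01, r16, r06 (baseline to 1 month, 1 to 6 months, baseline to 6 months) over a stated range.

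**Step 1: true variance.** A participant's change from baseline to visit t has variance 2v(1 − r0t). Averaging over n per arm and differencing two arms gives

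Var(true) = 4v(1 − r0t)/n.

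**Step 2: variance the model reports.** The random-intercept residual variance estimates v(1 − r̄), where r̄ is the mean of the three correlations. Both contrasts therefore receive

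Var(model) = 4v(1 − r̄)/n.

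**Step 3: ratio and error rate.**

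Model SE / true SE = √[(1 − r̄)/(1 − r0t)]

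Actual type I error = 2{1 − Φ(1.96 × ratio)}

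For 0.70/0.60/0.50 and v = 1, r̄ = 0.60:
- Model SE, both visits: √(4 × 0.40/308) = 0.0721.
- True SE at 1 month: √(4 × 0.30/308) = 0.0624, ratio 1.155.
- True SE at 6 months: √(4 × 0.50/308) = 0.0806, ratio 0.894.

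**Step 4: results over the assumed range.**

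| r01 / r16 / r06 | 1 − r̄ | 1-month SE ratio | 1-month type I error | 6-month SE ratio | 6-month type I error |
|---|---|---|---|---|---|
| 0.60 / 0.60 / 0.60 | 0.400 | 1.00 | 5.0% | 1.00 | 5.0% |
| 0.65 / 0.60 / 0.55 | 0.400 | 1.07 | 3.6% | 0.94 | 6.5% |
| 0.70 / 0.60 / 0.50 | 0.400 | 1.15 | 2.4% | 0.89 | 8.0% |
| 0.75 / 0.55 / 0.40 | 0.433 | 1.32 | 1.0% | 0.85 | 9.6% |

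A simulation with 308 per arm and 0.70/0.60/0.50 (4,000 runs) gave 2.3% at 1 month and 8.2% at 6 months, in line with the formula.

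**Step 5: patterns that break the direction.**
- 0.60/0.70/0.60: both ratios are 0.957, so both standard errors are too small.
- 0.65/0.60/0.55 with visit standard deviations 1, 1.2, 1: the ratios are 1.03 and 1.02, so both are slightly too large. Here the true variance is (variance at 0 + variance at t − 2 × covariance) × 2/n, and the model's residual variance is the pooled within-person variance.

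**Step 6: joint interaction test.** The Wald statistic on both interaction terms, using the model's covariance, is a weighted sum of two independent chi-squared variables with one degree of freedom each. The weights are the eigenvalues of (model covariance)⁻¹ × (true covariance). For the three declining patterns they are 0.856 and 1.144, 0.711 and 1.289, and 0.532 and 1.468. Comparison with the nominal 5% critical value gives type I errors of about 5.1%, 5.3% and 5.9%. The two contrast errors largely offset each other.

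**The case against.** The strongest reply has four parts.

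**Direction.** A reader might infer that the 6-month standard error is too small as a matter of fact. The article does not support that: it gives no correlations or variances, and Step 5 shows patterns in which both standard errors err the same way. This stands, and the conclusion has to be conditional.

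**Which test.** The article plans an interaction between group and categorical time and does not name separate 1-month and 6-month change contrasts as the tests. The joint test is nearly correct. With equal variances, the model's between-group difference in level at 6 months also has the right variance. This stands as well: the error lies in the single-visit change contrasts. Those are, however, the individual coefficients that such a model prints and that reports usually quote.

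**Another analysis exists.** The linear regression at the follow-ups, if fitted visit by visit, has no within-person covariance to misspecify, and it supplies the mean difference. A reader might take the repeated-measures model to be the sole or main test of mental-health safety. The article does not say so: mental health is one of several secondary objectives, and adverse events are assessed separately.

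**Detail left to the analysis plan.** The article is condensed, and it does not rule out a residual correlation structure. This stands in part. An unseen plan could add one, but the article states the participant intercept as its device for individual variability, and that stated choice is restrictive.

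A further tempting inference is that the wrong covariance removes the protection of a likelihood analysis when data are missing at random. That is too strong. Some bias is possible, but its size depends on dropout and correlations that the article does not give.

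**Conclusion.** The point holds in a conditional and limited form. As stated, and with independent residuals, the model forces equal variances and equal correlations on visits with unequal gaps. Under the assumed declining correlations, the 6-month change contrast is tested at about 6.5–9.6% instead of 5%, and the 1-month contrast at about 3.6–1.0%. These figures rest on equal variances, complete data and correlations chosen for illustration. If the true correlations and variances are equal there is no error at all.

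The primary outcome, the sample size and a visit-by-visit regression of the scores do not depend on this assumption. It is a minor point about a secondary analysis, worth acting on because the assumption is unsupported in the text and easily avoided.

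**What to change.** For PHQ-9 and GAD-7, replace the participant random intercept with an unstructured within-participant covariance over the three visits (three variances and three covariances), fitted by REML with site kept in the model. In R, nlme with a general correlation (corSymm) and visit-specific variances (varIdent) can keep site as a random intercept; the mmrm package would take site as a fixed effect. At minimum, keep the present model and report participant-clustered robust standard errors. Group, categorical time and their interaction stay as they are.

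It would also help to say whether the interaction will be judged by the joint test, by the contrast at each visit, or by both.

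The cost is a change of wording. Six covariance parameters are a negligible burden with 616 planned participants, no further data are needed, and the standard errors no longer depend on an assumed correlation pattern.

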**Measurements:**

The primary outcome is 7‐day point prevalence carbon monoxide‐validated abstinence, assessed six months after study enrolment or target quit date. Secondary outcomes include: 6‐month continuous abstinence defined by Russell Standard, self‐reported smoking abstinence at 1 month, ≥50% smoking reduction (cigarettes/day) at 1 and 6 months, mental health symptoms and general mood and physical symptoms at 1 and 6 months, cost‐effectiveness of the intervention and adherence to and satisfaction with the intervention.

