### Inclusion criteria

Participants will be included if they: (i) are aged ≥18 years; (ii) are self‐reported current cigarette smokers (in the past 7 days); (iii) have a diagnosis of mental illness (in accordance with UK NHS categorization, https://www.nhs.uk/mental-health/conditions/) and are currently being managed or receiving treatment for this in primary or secondary care, validated by their healthcare records; (iv) have the capacity to provide consent; and (v) are seriously considering quitting, cutting down or maintaining abstinence from tobacco.

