**Assessments**				
Socio‐demographic characteristics	x			
Nicotine dependence	x			
Motivation to quit	x			
Age started smoking	x			
Smoking duration	x			
Past year quit attempts	x			
Current use of tobacco products other than cigarettes	x			
Ever e‐cigarette use as smoking cessation aid	x			
AUDIT‐C	x			x
Physical activity	x			x
Fruit and vegetable consumption	x			x
Patient Heath Questionnaire‐9	x		x	x
Generalized Anxiety Disorder Scale‐7	x		x	x
7‐day point prevalence			x	x
Sustained abstinence				x
50% smoking reduction			x	x
CO breath sample				x
General mood and physical symptoms			x	x
Adverse events			x	x
Use of e‐cigarette			x	x
Healthcare service use	x		x	x
Health‐related quality of life	x			x

Socio‐demographic characteristics include age, sex, employment status, ethnicity, education, accommodation type and marital status.

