#### Follow‐up data collection

Follow‐up data at 1 month and at 6 months will be obtained: online, via a link sent to the participant email address; via telephone, with support from a trust/GP‐based researcher; or via a paper‐based postal return, depending on the participant's preference. Given the alternative scenarios of intervention delivery outlined above and the potential for bias in follow‐up data collection, we stipulate that if the intervention is delivered by a trust/GP‐based researcher, then an alternative trust/GP‐based researcher will conduct the follow‐up data collection. As self‐reported abstinence at the 6‐month follow‐up will be biochemically validated using the PICO smokerlyzer (https://www.bedfont.com/products/smokerlyzer), this will require an in‐person visit either at the clinical base or in participants' homes to obtain a CO breath measurement reading to verify this.

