#### Main outcomes

##### Primary outcomes measures

Self‐reported 7‐day point prevalence abstinence assessed 6 months after study enrolment or target quit date (for those who set a target quit date within 1 week of enrolment) and verified by exhaled breath CO < 10 ppm, which will be collected within 7 days of the 6‐month follow‐up assessment.

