Analyses of smoking‐related outcomes will follow the intention‐to‐treat principle. This means that all participants will be analysed in the groups to which they were originally assigned, regardless of whether they completed the study or adhered to the intervention. Following the Russell Standard [30], those participants who will be lost to follow‐up or who do not provide outcome data will be treated as people who smoke in the analysis. If the missing data mechanism is suspected to be missing at random (MAR), sensitivity analyses will be performed using multiple imputation and the last observation carried forward. MAR will be determined if significant differences are found between missing and observed data. If there are substantial changes in the results under different missingness assumptions this will also indicate MAR. A complete case and as‐treated analysis will also be conducted. The latter of which accounts for the fact that some in the control group may have used e‐cigarettes during the treatment period. In the event of a non‐significant difference between groups on primary and other outcomes, associated Bayes factors will be calculated using the method of Dienes to differentiate between evidence for no effect and data insensitivity [56], using the effect size from the sample size calculation as a prior and specifying a half‐normal distribution.

Two subgroup analyses will be conducted. The first to assess differences as a function of trust versus GP practice and the second to assess the impact of the change made in month 7 to the mode of delivery in the intervention arm. We do not pre‐specify subgroup analysis by severity of mental illness because of likely low recruitment of this population and associated limited power to detect effects.

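### Breath CO is scheduled only at 6 months, so last observation carried forward has no earlier verified value to carry and is not a valid robustness check of the CO-verified primary outcome

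*Protocol article*

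**What the plan says.** All references are to the protocol article.

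- **Primary outcome measures.** The endpoint is self-reported 7-day abstinence at 6 months with exhaled CO below 10 ppm, the sample being one "which will be collected within 7 days of the 6‐month follow‐up assessment".
- **Table 1.** The row "CO breath sample" is marked in the 6-month column only. The row for 7-day point prevalence is marked at 1 and 6 months.
- **Follow-up data collection.** There are two follow-up times: "Follow‐up data at 1 month and at 6 months will be obtained" online, by telephone or by post. Validation is tied to the later one ("As self‐reported abstinence at the 6‐month follow‐up will be biochemically validated using the PICO smokerlyzer") and needs an in-person visit "to obtain a CO breath measurement reading to verify this".
- **Abstract, Measurements.** The early measure is "self‐reported smoking abstinence at 1 month", with no mention of CO.
- **Analysis, under Primary analysis.** For smoking-related outcomes, participants without outcome data are counted as smoking. If missingness at random is suspected, "sensitivity analyses will be performed using multiple imputation and the last observation carried forward". Complete-case and as-treated analyses are also planned. The text neither exempts the primary outcome from LOCF nor says which value would be carried.

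**The concern.** LOCF needs an earlier measurement of the same quantity. Here the quantity is verified abstinence, and the verifying measurement is first taken at the endpoint itself. Whatever is carried for someone who left before 6 months is therefore a different variable.

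What is at stake is the value of one named robustness check. If LOCF carries baseline status, it agrees with the main analysis by construction, and that agreement says nothing. If it carries the 1-month report, it changes both the verification and the time point. That report falls around the end of the 4-week pod supply given to the intervention arm, and relapse after it would not be seen. A reader shown such a result as support for the primary finding would be misled about what had been tested.

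**Working it through.** **Structure.** Scheduled CO measurements before 6 months: 0. CO-verified values available to carry: 0. The candidate values are:

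| Participant | Value that could be carried | Consequence |
|---|---|---|
| Lost before 6 months | Baseline status (Inclusion criteria: all are smokers) | Identical to missing = smoking |
| Lost before 6 months, 1-month data present | 1-month self-reported 7-day abstinence | Unverified, and at the wrong time point |
| Answers the 6-month questionnaire, gives no breath sample | 6-month self-report | Right time point, unverified |

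No row yields a verified 6-month value.

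**The plan's own figures.** Sample size section: 5.0% against 13.1%, 308 per arm. Difference 13.1 − 5.0 = 8.1 points; risk ratio 13.1/5.0 = 2.62; both agree with the text. Odds ratio (0.131/0.869)/(0.05/0.95) = 2.86. Power at 308 per arm is 94.1% (92.2% with continuity correction), in line with the stated figure of more than 90%. None of this depends on LOCF.

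**Illustration if 1-month self-report is carried.** Take 5% and 13.1% as the rates under missing = smoking. Let *m* be the proportion missing at 6 months, *a* the share of those with 1-month data, and *s* their 1-month self-reported abstinence. In each arm:

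LOCF rate = main-rule rate + *m* × *a* × *s*

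The document gives none of *m*, *a* or *s*. Assumed ranges: *m* 10–30%, equal in both arms; *a* 50–80%; (*s* control, *s* intervention) of (5%, 13.1%), (10%, 20%) or (10%, 25%).

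| *m* | *a* | *s* control, intervention | Control | Intervention | Difference (points) | Risk ratio | Odds ratio |
|---|---|---|---|---|---|---|---|
| main rule | – | – | 5.0% | 13.1% | 8.1 | 2.62 | 2.86 |
| 10% | 50% | 5%, 13.1% | 5.25% | 13.76% | 8.5 | 2.62 | 2.88 |
| 20% | 80% | 10%, 25% | 6.6% | 17.1% | 10.5 | 2.59 | 2.92 |
| 30% | 80% | 10%, 20% | 7.4% | 17.9% | 10.5 | 2.42 | 2.73 |
| 30% | 80% | 10%, 25% | 7.4% | 19.1% | 11.7 | 2.58 | 2.95 |

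Worked line: 0.05 + 0.2 × 0.8 × 0.10 = 0.066 and 0.131 + 0.2 × 0.8 × 0.25 = 0.171. That adds 308 × 0.016 = 4.9 control and 308 × 0.04 = 12.3 intervention abstainers, none verified.

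Over the whole grid the difference runs from 8.5 to 11.7 points, the risk ratio from 2.42 to 2.62 and the odds ratio from 2.73 to 2.95. About 1–7 control and 2–18 intervention participants are added.

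**Direction.** The change in the difference is *m*·*a*·*s* (intervention) minus *m*·*a*·*s* (control), so its sign is not fixed. With 10% missing in the intervention arm and 30% in control, *a* = 80% and *s* of 20% and 10%, the change is 0.1 × 0.8 × 0.20 − 0.3 × 0.8 × 0.10 = 0.016 − 0.024 = −0.8 points. The difference then falls from 8.1 to 7.3.

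**The case against.** The opposing case has five parts.

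- **The LOCF sentence names neither the primary outcome nor the value carried, and an analysis plan not shown here may settle both.** It is true that nothing states that 1-month self-report enters the primary outcome. A reader might infer that it certainly would; the text does not support that. But the sentence sits under the primary analysis, covers smoking-related outcomes and exempts none, and no analysis plan can supply an earlier CO value.
- **A third value exists.** For someone who answers at 6 months without a breath sample, the last observation is the 6-month self-report, which is a sensible thing to analyse. This stands, so LOCF is not always empty or distorting. It does not help those lost before 6 months.
- **A bias towards the intervention is not established.** This stands. A reader might infer it from the timing of the pod supply and the early trends in the feasibility study. However, the document gives no missingness or 1-month rates for dropouts. With equal missingness the risk and odds ratios barely move, and with unequal missingness the difference can shrink.
- **Other checks are planned.** Multiple imputation, complete-case and as-treated analyses are listed, and self-reported continuous abstinence at 6 months is a secondary objective. So it cannot be said that the primary result would go unchecked.
- **LOCF is conditional and secondary.** This stands, and it limits the consequence to one sensitivity analysis. LOCF is also workable for outcomes self-reported at both visits.

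**Conclusion.** The point holds in limited form. For participants lost before 6 months, the measurement schedule gives LOCF no verified value to carry, so it cannot serve as a robustness check of CO-verified abstinence. This follows from Table 1 and the follow-up section alone and needs no assumed figure.

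The numerical effect does rest on assumptions. If 1-month self-report is carried and missingness is equal between arms, the risk difference moves from 8.1 to about 8.5–11.7 points, with little change in the risk and odds ratios. Other assumptions change the size and can reverse the direction. The main analysis, the sample size and the data collection are not affected. It is an inexpensive correction that should be made, not a threat to the primary conclusion.

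**What to change.** Drop LOCF, or restrict it to outcomes measured in the same way at 1 and 6 months, such as the reduction of at least 50% in cigarettes per day.

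For the primary outcome, replace it with a sensitivity analysis of self-reported 7-day abstinence at 6 months, regardless of whether a CO sample was given, and label the result as unverified. Alongside it, report by arm how many participants claimed abstinence at 6 months with CO below 10 ppm, with CO of 10 ppm or more, and with no sample. This is useful because the questionnaire can be answered remotely while the breath sample needs a visit, so some claimed abstainers may lack a sample.

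The cost is a change of analysis wording and one extra table, from data already scheduled. The downside is that the replacement relies on self-report in an unblinded trial, which is why it should remain a sensitivity analysis. It also says nothing about participants with no 6-month data at all; for them, the planned multiple imputation remains the relevant check.

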### Sample size

We aim to recruit 616 participants, with 308 participants asigned to each group. Pooling the results of the only three RCTs comparing e‐cigarettes with placebo e‐cigarettes [15, 35, 36] yielded an expected effect size of risk ratio (RR) = 2.01 for 6‐month abstinence rates. We consider this estimate to be conservative as most of these trials used older, less effective first‐generation e‐cigarettes. In fact, recently published trials comparing active treatment (NRT) with a modern third‐generation e‐cigarette in the context of stop‐smoking services [12] found a superior effect of e‐cigarettes on 6‐month abstinence rates of RR = 1.63. Based on established effect estimates for NRT versus placebo from high‐quality trials [37], findings from this trial therefore indirectly suggest that, compared with placebo/usual care, third‐generation e‐cigarettes (as will be used in this trial) may increase 6‐month abstinence rates by nearly threefold (RR = 2.62). Given the low abstinence rates in the control conditions observed in the feasibility study [26], we revised the expected abstinence rates in the control (standard care) group from 7.7% (based on previous trials with people with mental illness) [38, 39] to 5.0%. Based on the feasibility study results (finding an absolute risk difference of 9.5%) [26] and the fact that a modern e‐cigarette is used, we assume an effect estimate of RR = 2.62, as found in more recent trials, to be most appropriate. We therefore expect an absolute predicted risk difference of 8.1%, assuming 6‐month abstinence rates of 5% in the control group and 13.1% in the intervention (e‐cigarette) group. A sample of 616 participants (308 per group) would provide more than 90% power to detect this effect, with an alpha level of 0.05 in two‐tailed analysis. This sample size would also provide 80% power to detect a more conservative effect of RR = 2.32 (intermediary between effect estimates from older and effect estimates from more recent trials using modern e‐cigarettes), with an absolute predicted risk difference of 6.6% at the 6‐month follow‐up (5.0% for the control group vs 11.6% for the treatment group).

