### Analysis

Data will be analysed in R Studio, with the alpha value set to 0.05. Outliers will be assessed and then handled based on clinically meaningful thresholds. This means only values that are unlikely to represent true clinical conditions are flagged. If outliers are retained in the analysis, sensitivity analysis will be performed to determine their impact on the results. Baseline characteristics will be reported by each arm using descriptive statistics: means and standard deviations (SDs) for continuous numeric variables [unless skewed, in which case the median and the interquartile range (IQR) will be reported instead]; and frequencies and percentages for categorical variables. Numeric variables include most recent diagnosis and acute events. All other variables are treated as categorical.

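### Missing at random (MAR) cannot be determined by the two rules given, yet those rules decide whether smoking outcomes are multiply imputed

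*Protocol article*

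**What the plan says.** The missing-data paragraph is in the Protocol article, Analysis, under Primary analysis. It covers smoking-related outcomes and sets out four things.

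- Participants without outcome data count as smokers. This is unconditional.
- If the mechanism is suspected to be MAR, "sensitivity analyses will be performed using multiple imputation and the last observation carried forward".
- Two rules say how MAR is recognised: "MAR will be determined if significant differences are found between missing and observed data", and "If there are substantial changes in the results under different missingness assumptions this will also indicate MAR".
- Complete-case and as-treated analyses are planned with no such condition.

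The Analysis section opens "with the alpha value set to 0.05", which is presumably the level for the significance test in the first rule. The variables to be compared are not named, and a substantial change is not defined. No other section corrects or qualifies the rules.

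**The concern.** MAR is an assumption about how missingness relates to values nobody has seen, so the observed data cannot confirm it. Both rules treat it as something the data can show.

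The first rule rests on participants with and without data differing on recorded characteristics. That contradicts MCAR. It says nothing about whether, given those characteristics, missingness also depends on the unseen smoking status. MAR and MNAR both remain open, and a non-significant result does not show that missingness is harmless.

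The second rule takes movement of the result across assumptions as a sign of MAR. Movement shows that the conclusion depends on which assumption is chosen, and it favours none of them. Labelling it MAR points the reader to the assumption under which standard multiple imputation is valid, just when caution is needed.

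At stake is whether multiple imputation of the smoking outcomes appears at all, and how it is described. LOCF is also listed as an analysis to run under MAR, but it makes a different assumption: no change since the last observation.

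**Working it through.** **1. The plan's own figures.** Inputs from Sample size: "with 308 participants asigned to each group", "with an alpha level of 0.05 in two‐tailed analysis", and rates of "5% in the control group and 13.1% in the intervention". With the pooled-variance normal approximation, power = Φ{[Δ − 1.96√(2p̄(1−p̄)/n)] / √[(p₁(1−p₁)+p₂(1−p₂))/n]}.

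- 5% v 13.1%, n = 308: (0.081 − 0.0453)/0.0229 = 1.56, so 94.1% (92.2% with continuity correction). This agrees with the stated figure of over 90%.
- 5.0% v 11.6%: (0.066 − 0.0436)/0.0221 = 1.02, so 84.5% (80.8% with continuity correction). This reproduces the stated 80%.

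Neither figure depends on the MAR rules.

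**2. Rule 1 as a switch.** The protocol gives no missingness rates or covariate differences, so those below are assumptions. The test is a two-proportion z-test of missing v observed participants on one binary covariate with 50% prevalence, N = 616.

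Worked case, 20% missing and a 10-point difference: groups of 123 and 493; SE = √[0.25(1/123 + 1/493)] = 0.0504; 0.10/0.0504 = 1.98; power ≈ Φ(1.98 − 1.96) = 0.51. Simulation of 4,000 trials per cell gave:

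| Missing | Significant, 10-point difference | Significant, 15-point difference |
|---|---|---|
| 10% | 32% | 61% |
| 20% | 51% | 85% |
| 30% | 62% | 93% |
| 40% | 67% | 96% |

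With a 10-point difference, this one test stays silent in about 33% to 68% of trials where missingness truly is related to the covariate. Two further cases show the rule pointing the wrong way.

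- Under MCAR with ten independent covariates, at least one test is significant in 1 − 0.95¹⁰ = 40% of trials, and MAR is declared. Baseline measures lists more than ten variables.
- If missingness depends only on unseen smoking status, and that is unrelated to the covariate, one test is significant at its nominal 5%. This MNAR case is mostly missed.

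**3. Rule 2 as a discriminator.** Compare complete case with missing-equals-smoking, both unconditional, at true rates of 5% and 13.1%.

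- *MCAR, 25% missing in each arm.* Complete case: 8.1 points. Missing-equals-smoking: 0.75 × 8.1 = 6.1 points. Ratio 1/(1 − 0.25) = 1.33 (simulated 8.0 and 6.0).
- *MNAR, 90% of abstainers and 70% of smokers observed (assumed).* Complete case: 0.1179/(0.1179 + 0.6083) − 0.045/(0.045 + 0.665) = 16.2% − 6.3% = 9.9 points. Missing-equals-smoking: 11.79% − 4.50% = 7.3 points. Ratio 1.36.

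The shift is nearly the same under two mechanisms, neither of which is MAR in the sense the rule intends. It cannot indicate MAR.

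**4. LOCF.** The primary outcome requires CO verification, and Table 1 schedules the CO sample only at 6 months. If LOCF is applied to that outcome, the only follow-up value available to carry forward is an unverified 1-month self-report.

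**The case against.** Several points on the other side stand.

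- **The check on missing-equals-smoking is not lost.** A reader might infer that the rule removes all scrutiny of the primary result. It does not: complete-case and as-treated analyses are planned regardless, and only multiple imputation and LOCF can be skipped. Complete case does not fully replace imputation, since it makes no use of 1-month smoking status or other predictors from participants without a 6-month outcome.
- **The circularity is partial.** It is tempting to call the second rule circular, because imputation needs MAR to be suspected first. But missing-equals-smoking and complete case are two missingness assumptions already available without that condition. The circle closes only so far as the rule relies on the conditional analyses.
- **The skip rates are for one test.** The rules are alternatives, many baseline variables could be compared, and an 8.0 v 6.0 point shift might be called substantial. The word suspected also leaves room for judgement. No skip rate for the combined rule can be derived from the document.
- **Bias from unequal follow-up is a different matter.** Missing-equals-smoking multiplies the responder risk ratio by (1 − m_I)/(1 − m_C), where m_I and m_C are the missing proportions in the intervention and control arms; an assumed 20% v 30% missing gives 0.80/0.70 = 1.14. A reader might attribute that to the MAR rule. It comes from the Russell Standard convention and would be the same under a perfectly worded paragraph.
- **LOCF may not be meant for the primary outcome.** The paragraph covers smoking outcomes generally, including self-reported reduction at 1 and 6 months. Any figure for LOCF bias would need 1-month abstinence rates that the document does not give, so none is offered.

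An unseen analysis plan may hold imputation details. It does not rescue the two rules, which are stated wrongly here rather than left out.

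**Conclusion.** The point holds: both rules are statistically wrong as written, and nothing elsewhere in the protocol corrects them. If followed, a data-dependent test decides whether the smoking outcomes are multiply imputed, and sensitivity to assumptions is recorded as support for one of them.

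The reach is limited. The missing-equals-smoking primary analysis, the complete-case and as-treated analyses, the sample size and the power are unchanged. The 32% to 67% range rests on an assumed 10-point difference, one binary covariate and 10% to 40% missing; it shows that the switch is unreliable and is not a forecast for this trial. The 1.33 v 1.36 comparison rests on assumed observation rates. The logical error depends on none of these figures. This is something that should be fixed, and it does not invalidate the primary analysis.

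**What to change.** 1. Delete both sentences on how MAR is recognised. A comparison of participants with and without outcome data can stay as description, with nothing conditional on it.
2. Run multiple imputation of the smoking outcomes whatever any test shows. State MAR as its assumption, and use arm, baseline predictors and 1-month smoking status. The Economic evaluation section already plans multiple imputation without a MAR condition, so this aligns the two.
3. Add a simple delta (tipping-point) range: multiply the odds of abstinence among missing participants by a factor from 1 (MAR) down to 0 (missing-equals-smoking), varied separately by arm, and report where the conclusion changes. The grid can be left to the analysis plan.
4. Drop LOCF for the CO-verified primary outcome. If it is kept for self-reported outcomes, describe it by its own assumption and not as an analysis under MAR.

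The cost is revised wording and a few extra model runs. No new data are needed. The change should be made before allocation is unblinded.
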